### Data handling

Data, including the number of patients screened, approached and interested in taking part, will be collected via a log completed by staff conducting screening. Trial data for individual participants will be collected by each Principal Investigator (PI) or their delegated person and recorded in the electronic case report form (eCRF) for the trial. Participant identification within the eCRF will be through a unique trial identifier number. A record linking the participant’s name to the unique trial identifier number will be held only in a locked room at the trial site, and is the responsibility of the PI. As such, participants cannot be identified from eCRFs. The Chief Investigator (CI) or delegated person will monitor completeness and quality of data recording in eCRFs and will correspond regularly with site PIs (or their delegated team member) with the aim of capturing any missing data where possible, and ensuring continuous high quality of data. No participant identifiable data will leave the study site. The quality and retention of study data will be the responsibility of the CI. All study data will be retained in accordance with the latest directive on Good Clinical Practice (GCP) and local policy.

All trial data will be stored securely in accordance with GCP, and the Sponsor and Newcastle Clinical Trials Unit (CTU) Standard Operating Procedures (SOPs). Any personal identifiable information will be stored at the study site for 10 years before secure disposal. Data will be handled, computerised and stored in accordance with the Data Protection Act 2018.

## Discussion

The outlook for patients diagnosed with RA now is vastly different compared with 30 years ago. With rapid access to diagnosis and treatment, a large proportion of patients with a new RA diagnosis can hope to achieve remission or low disease activity [19]. The widespread use of methotrexate and other disease modifying drugs has changed the face of this chronic disease, which traditionally resulted in chronic pain and disability. More recently, the advent of biologic drugs has transformed the treatment of those with moderate to severe disease, allowing many patients to continue their normal lives [20]. However, a large portion of patients who achieve remission, subsequently flare. The unpredictable nature of flares can cause disruption in home and working lives, and there is a well-documented association between rheumatoid arthritis and levels of anxiety and depression [21]. This unpredictability also makes the scientific investigation of flares very difficult. There is a gap in our knowledge of what triggers flares, and what pathophysiological changes happen during the flare process. RA is just one example of an immune-mediated relapsing remitting disease. If more was understood about the process of flare in RA, it could help to inform disease flares in other IMIDs such as multiple sclerosis, inflammatory bowel disease and psoriasis.

Our previous study investigating the biomarkers of remission in rheumatoid arthritis (BioRRA study) studied a similar cohort of patients, half of whom flared over a 6-month period [5]. This finding is comparable with other similar studies into remission and flare [13, 14, 22]. There is always an ethical consideration in a study of this nature, given that patients who are previously well, with their disease in remission, are asked to stop their medication. However, experience and our prior work tell us that a significant number of patients are keen to do this [23]. When consulting with our Newcastle Patient and Public Involvement (PPI) group in the planning stages, there was great appetite for such a study. Patients might be experiencing side effects from their medication, or the undesirable need for ongoing blood tests. Some patients simply do not wish to take a medication regularly, particularly if their disease has been quiescent for years, as they may feel the medication is not needed. As a speciality, rheumatologists are becoming more familiar with withdrawing medications when patients are in remission, and indeed, DMARD minimisation (though not necessarily complete cessation) in the setting of RA remission is now supported by current RA management guidelines issued by the American College of Rheumatology (ACR) [24], and the European Alliance of Associations for Rheumatology (EULAR) [25].

The design of the BIO-FLARE study allows a participant to be closely monitored in the period immediately prior to clinical onset of flare. Clinical determinants are collected and tracked over time, such as CRP, joint counts and RAPID-3 scores, along with biological outcomes. At each participant visit, blood is taken for research, processed following SOPs and stored, with the sample location information recorded in a laboratory inventory management system (LIMS). The downstream analysis of this blood will allow multiple questions to be explored. Epigenetic profiling of PBMCs and CD14+ monocytes will be conducted allowing comparison to those who stay in remission. Whole blood and PBMCs will be analysed by flow cytometry to provide deep immune-phenotyping of the samples. Serum and urine samples will be used for metabolic profiling, and autoantibody profile and cytokine levels will also be investigated using serum samples. Synovial tissue collected at the point of flare will be analysed and, in certain cases, can be paired with samples from the same participant whilst in remission, prior to DMARD cessation.

The impact of the SARS-CoV-2 pandemic has had far reaching consequences for all aspects of medical care, including non-COVID research. After extensive discussions amongst the Trial Management Group, including statisticians, the decision was made to close recruitment at 118 participants to enable timely data analysis. Strategies to lessen the impact caused by the reduced sample size on power will be considered including, for example, restricting the number of biomarkers to be considered in a multivariable risk model.

In summary, the novel nature of this study will allow deep interrogation of the mechanisms occurring in the days and weeks leading up to the point of RA flare. Our aim is to further the understanding of the pathophysiology of flare, develop strategies for intervention, and also to prevent or predict flare. Furthermore, these same mechanisms may also be at play during the onset of RA, and thus may also serve to further our understanding of the immunopathology of early stages of the disease.

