**Methods:**

The BIO-FLARE study is a non-randomised longitudinal cohort study that aims to enrol 150 patients with RA in remission on a stable dose of non-biologic disease-modifying anti-rheumatic drugs (DMARDs), who consent to discontinue treatment. Participants stop their DMARDs at time 0 and are offered an optional ultrasound-guided synovial biopsy. They are studied intensively, with blood sampling and clinical evaluation at weeks 0, 2, 5, 8, 12 and 24. It is anticipated that 50% of participants will have a disease flare, whilst 50% remain in drug-free remission for the study duration (24 weeks). Flaring participants undergo an ultrasound-guided synovial biopsy before reinstatement of previous treatment. Blood samples will be used to investigate immune cell subsets, their activation status and their cytokine profile, autoantibody profiles and epigenetic profiles. Synovial biopsies will be examined to profile cell lineages and subtypes present at flare. Blood, urine and synovium will be examined to determine metabolic profiles. Taking into account all generated data, multivariate statistical techniques will be employed to develop a model to predict impending flare in RA, highlighting therapeutic pathways and informative biomarkers. Despite initial recruitment to time and target, the SARS-CoV-2 pandemic has impacted significantly, and a decision was taken to close recruitment at 118 participants with complete data.

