### Follow-up period – day 14, 35, 56, 84, 168 and ad hoc visits

At routine visits, adverse event recording and current medications are noted. Clinical and research blood and urine tests are taken and questionnaires are completed. A joint examination is performed to allow calculation of a DAS28-CRP.

If a participant feels that their arthritis is becoming more active during the follow-up period, then they can arrange an ad hoc visit. These visits follow the same format as the routine visits.

At any point in the study period if the participant is found to have a DAS28-CRP ≥ 3.2 they are defined as having a confirmed flare. If a participant is found to have a DAS28-CRP ≥ 2.4 but < 3.2 they will return for a further ad hoc assessment within 14 days. At the second assessment if the DAS28-CRP ≥ 2.4 they will be defined as a confirmed flare (Fig. 3).

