### Confirmed flare

If a participant has a confirmed flare (DAS28-CRP ≥ 3.2, or DAS28-CRP ≥ 2.4 on 2 occasions within 14 days) an ultrasound-guided synovial biopsy will be arranged to take place within 7 days of flare confirmation. Following the synovial biopsy, the participant will receive glucocorticoid therapy if needed, and will be discharged from the study back to their referring team to rapidly recommence DMARDs. A further review (telephone call or face to face visit) will occur 4 weeks after a confirmed flare to ensure the participants’ RA is back under control, that they have had contact with their referring rheumatology team, and that they have resumed DMARD therapy. No study data will be collected at that visit.

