### Statistical considerations

The aims of the statistical analyses are to estimate and understand the longitudinal stochastic relationship between the risk of flare and each of the markers in the relevant biological pathways. The overall proportion (confidence interval) of participants who flare by 24 weeks will be estimated using the actual time of flare based on Kaplan-Meier estimates. Graphical representation and descriptive statistics of the longitudinal marker measurements will indicate trends in markers over time, to identify plausible differences in trends in participants who flare and those who do not.

The association between markers and risk of flare will be investigated in a series of descriptive univariate models, based on analysis of each covariate in Cox proportional hazards models, or parametric alternatives, with time varying covariates to account for the longitudinal nature of marker data, through attributing variability at the participant level, time level and marker level. Individual covariates may not be linear in their relationship with outcome so the ‘best’ fitting non-linear relationship will be explored using Fractional Polynomial transformation [18]. The magnitude of the relationship of each marker with risk of flare will be described using estimated beta coefficients (with confidence intervals) accounting for variability at the time level and marker level.

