## Abbreviations

ACPA: Anti-citrullinated peptide antibody
ACR: American College of Rheumatology
CI: Chief Investigator
CRP: C-reactive protein
CTOC: Combined Trial Oversight Committee
CTU: Clinical Trials Unit
DAS28-CRP: Disease Activity Score using 28 joint count and CRP
DMARD: Disease modifying anti-rheumatic drug
eCRF: Electronic case report form
ESR: Erythrocyte sedimentation rate
EULAR: European Alliance of Associations for Rheumatology
FBC: Full blood count
GCP: Good clinical practice
HAQ-DI: Health assessment questionnaire-disability index
HRA: Health research authority
IMID: Immune mediated inflammatory disease
LFT: Liver function tests
LIMS: Laboratory inventory management system
MFI: Multidimensional fatigue inventory
PBMC: Peripheral blood mononuclear cell
PI: Principal investigator
PPI: Patient and public involvement
RA: Rheumatoid arthritis
RA-FQ: Rheumatoid arthritis flare questionnaire
RAPID-3: Routine assessment of patient index data-3
REC: Research Ethics Committee
RhF: Rheumatoid factor
SOP: Standard operating procedure
TMG: Trial Management Group
UE: Urea, electrolyte and renal profile

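### Flare is a cut-off on DAS28-CRP, so the score's components, and markers that only track them, can be linked to flare through the formula; report value added beyond previous-visit DAS28-CRP

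*Protocol article*

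**What the plan says.** **Outcome.** The Confirmed flare section defines flare as "DAS28-CRP ≥ 3.2, or DAS28-CRP ≥ 2.4 on 2 occasions within 14 days". The Abbreviations expand the score as "DAS28-CRP: Disease Activity Score using 28 joint count and CRP", and the Follow-up section says "A joint examination is performed to allow calculation of a DAS28-CRP". The Clinical discretion section accepts that infection or trauma can push the score over the remission cut-off by raising inflammatory markers or the patient visual analogue scale.

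**Model inputs.** The Abstract (Methods) says "Taking into account all generated data, multivariate statistical techniques will be employed to develop a model to predict impending flare in RA". The Discussion says "Clinical determinants are collected and tracked over time, such as CRP, joint counts and RAPID-3 scores, along with biological outcomes". The Statistical considerations describe the aim more narrowly, as "the longitudinal stochastic relationship between the risk of flare and each of the markers in the relevant biological pathways". They plan univariate Cox (or parametric) models with time-varying covariates and state no lag between the covariate value and the flare. Table 1 schedules CRP and DAS28-CRP at every follow-up visit, including the ad hoc visits at which flare may be declared.

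**Purpose and size.** The primary objective is to measure immune dysregulation just before flare. The model is meant to point to therapeutic pathways and informative biomarkers. Recruitment closed at 118, with half expected to flare, and the Discussion considers limiting how many biomarkers enter the multivariable model.

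**The concern.** When the event is a threshold on a score, whatever enters the score is associated with the event through arithmetic alone. A Cox model with time-varying covariates and no lag uses the value current at the event time. For CRP or a joint count, that is the value that helped declare the flare. A laboratory marker that adds nothing of its own but moves with CRP inherits part of the same link.

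At stake is interpretation. A hazard ratio or C-index that partly reflects the make-up of DAS28-CRP could be read as evidence about what drives flare. With about 59 flares (118 × 0.50), the multivariable model can hold few terms, so it matters which associations count as biology.

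**Working it through.** The article gives no figure to reproduce on this point. The question is how large an association the formula alone can create.

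**Inputs from the article:** 118 participants; about 59 flares; follow-up at days 14, 35, 56, 84 and 168; remission below 2.4; flare at 3.2 or above, or two readings of 2.4 or above.

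**Assumptions:** the DAS28-CRP weights are not printed. Simulations B and C assume the standard weights; A does not use them. Serial correlations are assumed throughout.

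**Scale of one component.** With an assumed CRP term of 0.36 × ln(CRP + 1), a rise from 3 to 30 mg/L adds 0.36 × (ln 31 − ln 4) = 0.36 × 2.05 = 0.74. With half that weight it adds 0.37. The two cut-offs are 3.2 − 2.4 = 0.8 apart. With assumed joint weights of 0.56 and 0.28, a first tender and swollen joint adds 0.56 + 0.28 = 0.84.

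**Simulation A (equal weights).** The score is the sum of four independent normal components. One threshold, set to give 50% flares, serves for both entry and flare. N = 118, five follow-up visits, 400 trials per setting. One component is entered in a time-varying Cox model.

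| Visit-to-visit correlation | Flare-visit value: median HR per SD, share with p < 0.05 | Previous-visit value: median HR per SD, share with p < 0.05 |
|---|---|---|
| 0 | 2.5, 100% | 1.00, 6% |
| 0.3 | 2.5, 100% | 1.19, 23% |
| 0.6 | 2.3, 100% | 1.38, 63% |

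**Simulation B (assumed standard weights).** Independent components, the article's entry and flare rules, N = 118, 200 runs in each of three scenarios with flare rates of 19% to 28% (about 22 to 33 flares).
- Flare-visit CRP: HR 1.5 to 1.8 per SD, significant in 73% to 81% of runs.
- Previous-visit CRP: HR 1.07 to 1.43, significant in 5% to 40%.

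**Simulation C (assumed standard weights, flare rates of 17% to 59%, so spanning the anticipated 50%).** No flare process beyond the score itself.
- Flare-visit CRP: HR 1.9 to 2.5 per SD, significant in 95% to 100% of runs.
- Previous-visit CRP: HR 1.2 to 1.8, significant in 18% to 69%.
- A marker linked to flare only through a 0.6 correlation with CRP, at its previous-visit value: significant in 10% to 34%.
- The same marker after adjustment for previous-visit DAS28-CRP: 3% to 5%, about the nominal rate.

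**Reading.** At the flare-defining visit the association is near-certain, even where the earlier value carries no information. One visit earlier it is partial. It vanishes without serial correlation and grows as serial correlation rises. Adjusting for the earlier score removes what a mere correlate of CRP inherits.

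**The case against.** The strongest reply is that the article never says CRP or joint counts go into the model. The Discussion sentence describes monitoring. The Abstract phrase follows a list of laboratory assays and may mean only those. The Statistical considerations speak of markers in biological pathways. The candidate list, the lag and any benchmark model commonly belong in an analysis plan, which is not shown. Much of this stands: the absence of a candidate list or lag is not the point here. What remains is that the Abstract's statement of model input is broad as worded, that unlagged time-varying models do not guard against the problem, and that the problem also reaches laboratory markers that follow CRP, which the narrower reading leaves in.

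A second reply is that an earlier CRP or joint count is a legitimate predictor, since a person nearer the cut-off really is at higher risk of the defined event. This also stands. It is why earlier values should not simply be barred, and why the remedy is a benchmark.

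Three stronger readings are tempting and not supported:
- A reader might infer that CRP and joint counts are bound to emerge as predictors by construction. That is close to true only for flare-visit values. At the previous visit, significance fell as low as 5% to 6% of runs.
- A reader might infer that RAPID-3 shares an item with DAS28-CRP. The article gives the contents of neither score in enough detail to show it.
- A reader might infer that components will crowd biological markers out of the final model. No selection procedure is stated, and this was not simulated.

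**Conclusion.** The point holds in a limited form. Because flare is a DAS28-CRP threshold, CRP, joint counts, the patient scale and markers that only track them can be associated with flare through the formula. The link is near-certain for values from the flare-defining visit (73% to 100% of runs significant, HR 1.5 to 2.5 per SD). It is partial for previous-visit values (5% to 69%, HR 1.00 to 1.8). The article's wording does not guard against it, though it does not expressly make these items covariates.

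The sizes rest on independent components, assumed weights (equal in A, standard in B and C), assumed serial correlations and, for the proxy marker, an assumed correlation of 0.6. Simulation B's flare rates lie below the anticipated 50%. The direction is the same in all three simulations; the exact percentages should not be carried over to the real data. This is a worthwhile improvement to how results are analysed and claimed, and does not show that the planned model is circular.

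**What to change.** 1. Narrow the Abstract's statement of model input: DAS28-CRP components measured at the flare-defining visit are not candidate biomarkers. State how flares confirmed on two readings are handled, because there the visit before confirmation is itself part of the definition.
2. Fit previous-visit DAS28-CRP once as a clinical benchmark.
3. Report each pre-flare marker, and the final model, both unadjusted and as added value beyond the benchmark (likelihood-ratio test, change in C-index).
4. Rest pathway and biomarker claims mainly on the added value.

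**Cost.** A change of wording and one extra model, using data that Table 1 already collects. Headline performance will look less favourable. Adjustment may also remove part of a true effect that acts through CRP or the joints, which is why both results should be shown.

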## Data Availability

Not applicable

## Abbreviations

ACPA: Anti-citrullinated peptide antibody
ACR: American College of Rheumatology
CI: Chief Investigator
CRP: C-reactive protein
CTOC: Combined Trial Oversight Committee
CTU: Clinical Trials Unit
DAS28-CRP: Disease Activity Score using 28 joint count and CRP
DMARD: Disease modifying anti-rheumatic drug
eCRF: Electronic case report form
ESR: Erythrocyte sedimentation rate
EULAR: European Alliance of Associations for Rheumatology
FBC: Full blood count
GCP: Good clinical practice
HAQ-DI: Health assessment questionnaire-disability index
HRA: Health research authority
IMID: Immune mediated inflammatory disease
LFT: Liver function tests
LIMS: Laboratory inventory management system
MFI: Multidimensional fatigue inventory
PBMC: Peripheral blood mononuclear cell
PI: Principal investigator
PPI: Patient and public involvement
RA: Rheumatoid arthritis
RA-FQ: Rheumatoid arthritis flare questionnaire
RAPID-3: Routine assessment of patient index data-3
REC: Research Ethics Committee
RhF: Rheumatoid factor
SOP: Standard operating procedure
TMG: Trial Management Group
UE: Urea, electrolyte and renal profile
